## 4. Discussion

The study will be randomized and will examine the characteristics of the trapezius and pectoralis major muscles, respiratory function, stability, and overall posture in children and adolescents with PE before and after a tailored physical therapy program lasting three months. The assessment of study participants will include four different testing methods: myotonometry, cardiopulmonary exercise testing (CPET), posture evaluation, and static balance analysis.

An excessively high position in the upper chest area may cause PE, and the pectoralis major muscle has a biomechanical role in lifting the sternum [25]. Consequently, the main hypothesis of this investigation will focus on assessing the tone of the pectoralis major and trapezius muscles, as well as examining any recorded discrepancies that might contribute to this condition. The study will explore changes in length, elasticity, muscle tone, and relaxation in muscles potentially involved in the development of the pathology through a non-invasive measurement method: myotonometry. No studies have been found in the literature that evaluate the properties of muscles involved in the development of PE. However, some evidence links thoracic kyphosis with this condition [6], prompting an analysis of the literature’s reported changes and a comparison with the findings of this study. Thoracic kyphosis appears as limited mobility of the thoracic spine caused by alterations in both non-contractile and contractile tissues [26].

Therefore, in a study conducted by Yeo et al., muscle tone was evaluated in the upper trapezius and pectoralis major muscles of patients with thoracic kyphosis using MyotonPro^®^ (Myoton AS, Tallinn, Estonia). Variations in the examined parameters were observed [27]. The measurement technique used in this study is similar to that in our research, with the MyotonPRO^®^ tip positioned vertically at the midpoint of the subjects’ upper trapezius and pectoralis major muscles.

The CPET evaluation of the study participants will assess the effect of sternal deformity on cardiopulmonary function and compare the results with those reported in existing literature.

Similarly to our study, Tariq Abu-Tair et al. evaluated these factors in 2018 through a study involving 99 children with pectus excavatum using CPET on a treadmill. Based on the measured Haller index, the results of CPET testing in children with mild and moderate pectus excavatum showed that cardiopulmonary function depends more on the individual’s level of exertion, and that cardiopulmonary capacity varies widely, from normal to moderate. Additionally, even among patients with a Haller index below 3.25, fewer than 15% exhibited moderate functional impairment of the cardiopulmonary system. The study’s findings indicated that the severity of sternal deformity correlates with its effect on cardiopulmonary function, with variations observed in heart rate and cardiac output. Specifically, there is an initial increase in heart rate at the anaerobic threshold, followed by a decline in stroke volume at both the anaerobic threshold and at maximum stroke volume, ultimately leading to a decrease in cardiac output due to the severity of the sternal deformity [28].

An abnormally low maximum anaerobic VO_2_ during exercise testing is a common finding reported by other studies that have documented cardiac dysfunction due to pectus excavatum. Using a treadmill for cardiopulmonary exercise testing, patients with pectus excavatum could not reach the vascular volumes of healthy control subjects at any exercise intensity. Furthermore, their low cardiac output limited their maximum exercise capacity [29,30].

Tiffany J. Zens et al. assessed 261 patients with pectus excavatum through cardiopulmonary exercise testing (CPET) using an ergometric bicycle, revealing that 33% of patients showed reduced aerobic capacity. The study found that the severity of PE correlates with dysfunction of both right and left ventricular systolic function and may also impact exercise tolerance [31].

Using an ergometric bicycle to perform CPET on 259 subjects with pectus excavatum and an average age of 15.8, [32] study asserts that ventilation disorders are not associated with exertional dyspnea or decreased aerobic fitness in patients with this deformity.

Investigating these aspects and comparing the results with those reported is motivated by the similarities and differences observed in CPET testing in children with pectus excavatum in the studies mentioned earlier, regardless of whether the tests were performed on an ergometric bicycle or a treadmill.

The GaitOn posture assessment is among the evaluation tools used in this study. Current practice notes that children and adolescents with PE also experience posture issues in their limbs and spine. Published studies support these observations, showing that these children tend to have a lower body weight [32] and poorer posture [33,34]. It is advisable to assess the spine for thoracic kyphosis, lumbar lordosis, pelvic tilt, and lateral tilt angles in the thoracic, lumbar, and pelvic regions, then refer patients to medical rehabilitation centers for correction [34]. The evaluation of posture in children and adolescents with PE is expected to show improvement in the identified parameters after three months of physical therapy.

Since no information on these aspects has been found in the literature, the evaluation of static balance (stabilometry-PoData) will be the fourth method used in this study to assess children with pectus excavatum.

Static balance in children with thoracic hyperkyphosis is affected by removing specific visual input and is linked to changes in the contraction and strength of certain trunk and lower extremity muscles [35].

Contrary to these observations, there are studies on young individuals with postural thoracic kyphosis that show no significant relationship between body balance and thoracic kyphosis [36]. These aspects will be assessed and analyzed in the current study. To help design an individualized exercise program and support one of the established conclusions, the static balance parameters of children and adolescents with PE at the end of the physical therapy program will be compared with the initial parameters, and the results will be analyzed.

A combined exercise program effectively corrects spinal deviations [37] and improves balance in adolescents with postural kyphosis [38].

Davi DE Podestá Haje et al. also highlight the importance of physical activity in children and adolescents with mild to moderate PE. A study involving participants who performed targeted exercises to strengthen the anterior chest muscles at least five times a week, under the supervision of a physical therapist and with controlled breathing, considered various factors, including patient age and compliance with the program. The results demonstrated the exercises’ effectiveness in correcting or partially correcting pectus excavatum, especially when therapy began early in cases of milder and more flexible deformities. The exercise regimen used by participants included simultaneous resistance-free abduction and extension of the upper limbs, trunk extension while lying down, push-ups, sit-ups, and blowing up a balloon for 10 min [39].

In a 2020 study, Nuray Alaca et al. recommended kinetotherapy, which includes cardiopulmonary exercises and chest muscle toning, for patients with pectus excavatum. The physical therapy program involved breathing exercises for each lung lobe, upper and middle/lower diaphragmatic lateral rib breathing exercises, and exercises for the musculoskeletal system that included postural awareness, trunk mobilization and manipulation, stretching, strengthening, and additional aerobic exercises [11].

The proposed exercise program, although similar to those described in previous studies and detailed in the Materials and Methods section, is unique because it is performed daily for three months and tailored individually based on parameters identified during the initial assessments.

The effect of the three-month exercise program on children and adolescents with PE will be studied in relation to deformity progression. The evaluated parameters will be correlated, and the findings compared with existing research to aid in developing an assessment and rehabilitation protocol for these patients.

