### 2.1. Sample Size Calculation

The effect size was 0.5, the type I error was α = 0.05, and power was 0.8. A total sample size of at least 35 patients was required. The sample size was calculated using G*Power 3.1.9.7 (Universitat Kiel, Kiel, Germany) with the Wilcoxon signed-rank test (matched pairs)

The within-group analyses will evaluate the effects over time. The evaluation of effect size was based on Cohen’s conventions for large effects [14]. The total sample size of our study (at least 35 patients) is in accordance with that calculated by Zielinski for patients who followed kinesiotherapy with the same statistical power and effect size (36 patients) [15].

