### 2.3. Exercise Program

Following the parameters obtained during the initial assessment, the physiotherapist will develop a personalized exercise plan tailored to the patient’s needs.

At this stage, the physiotherapy program is designed and learned under the guidance of the physical therapist (2 weeks, 5 sessions per week, 60 min per session) and continued at home daily for three months. During the 10 physiotherapy sessions with the specialist, the patient carefully and correctly learns the exercises to perform at home in the next phase.

The objectives of the exercise program are to correct upper trunk posture, straighten the spinal column, increase mobility, re-educate muscles (by strengthening paravertebral muscles and relaxing muscles in the anterior thoracic area), and prevent or correct secondary axial deviations. Additionally, it aims to improve respiratory function and properly manage breathing during exercise.

The program includes exercises for spinal and rib cage mobility, exercises for toning the extensor trunk muscles (focusing on strengthening the back muscles and relaxing or stretching the front trunk muscles), respiratory re-education exercises, and exercises for stability re-education. To understand the program, Table 1 provides a detailed description of the exercises specifically designed by the authors in a potential work plan.

Proposed exercise plan for patients with PE and secondary axial deviations:

**Table 1 life-15-01624-t001:** Proposed exercise plan for patients with PE.

	Medical Rehabilitation Center	Home Exercise
Exercise Description	Number of Repetitions Week 1–2	Number of Repetitions Week 3–12
***Exercise 1:*** Patient sitting on a Bobath ball, feet on the ground, knee and hip joint, upper limbs placed behind the cervical spine with palms in contact with the cervical spine and arms close to the ear. The patient brings the arms back with an inhale, holds the position for 3–5 s and returns to the starting position with an exhale. (Figure 1a,b)	10 repetitions × 2 sets	10 repetitions × 3 sets
***Exercise 2:*** The patient on the Bobath ball, seated as in the previous exercise, positions the hands under the mandible parallel to the ground, and brings the arms backwards with double extension while inhaling, and then forward while exhaling.	10 repetitions × 2 sets	10 repetitions × 3 sets

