### 2.5. Statistical Analysis

Statistics will be performed using GraphPad Prism 5.0 for Windows. The descriptive statistics will be computed for all variables (mean and standard deviation). Before statistical applications, the normal distribution of values will be verified by the D’Agostino-Pearson normality test. The intragroup data (analyzed parameters at baseline and after the physical exercise program) will be compared with the paired *t*-test.

For the myotonometry, frequency, stiffness, decrement, stress relaxation time and creep of the trapezius and major pectoralis will be compared before and after the 3-month physical exercise program. VE and VO_2max_ will be analyzed at baseline and after the physical exercise program. Paired *t*-tests will be used to compare the intragroup data of the postural stability parameters (stabilometry data in the different testing situations). GaitOn postural analysis parameters will be measured before and after the 3-month physical exercise program.

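### The before-after balance comparison cannot support either side of the kyphosis-balance literature that the Discussion asks it to address

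*Protocol article*

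**What the plan says.** Section 4 (Discussion) of the protocol article first cites evidence that static balance is affected in children with thoracic hyperkyphosis. It then sets against this studies of young people with postural kyphosis that "show no significant relationship between body balance and thoracic kyphosis [36]. These aspects will be assessed and analyzed in the current study". The next sentence gives the means: "To help design an individualized exercise program and support one of the established conclusions, the static balance parameters of children and adolescents with PE", measured when the programme finishes, are to be set against the baseline values.

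Section 2.5 fixes the test: "Paired *t*-tests will be used to compare the intragroup data of the postural stability parameters", in each of the stabilometry testing situations. No posture measure, covariate or grouping factor enters that comparison.

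Three other places mention correlation:
- Section 2.4 says the recorded parameters will be analysed for correlation.
- Section 3 says, of stabilometry, that the aim includes possible correlations once posture has been corrected.
- Section 4 says near its end that the evaluated parameters will be correlated.

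None names a pair of variables. For posture, section 2.4.4 lists C7 as the only spinal marker in the lateral view, and section 3 names the shoulder angle as the targeted lateral measure. No kyphosis angle is named.

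**The concern.** Whether kyphosis is related to balance is a question of association between two measurements across patients. Whether balance changes over three months of exercise is a question about the mean of one measurement within patients. The Discussion offers the second as the means of settling the first.

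A significant improvement in balance could come from the exercises, from growth, or from familiarity with the platform, and in a single group these cannot be separated. None of them requires kyphosis to matter for balance. A non-significant change does not show that kyphosis and balance are unrelated. The null side needs particular care, because one of the two cited findings is itself a statement of no significant relationship, which a non-significant balance test could appear to confirm.

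At stake is one interpretive statement in the eventual report. The main objective (respiratory function and posture), the sample size, the data collected and the balance test itself are unaffected.

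**Working it through.** **1. What the study is sized for.** Inputs from section 2.1: design values, "The effect size was 0.5, the type I error was α = 0.05, and power was 0.8"; resulting number, "A total sample size of at least 35 patients was required"; calculated "with the Wilcoxon signed-rank test (matched pairs"). Sidedness is not stated; two-sided is assumed.
- For the Wilcoxon test with normally distributed differences, the effective n is 35 × 3/π = 33.4.
- The noncentrality is 0.5 × √33.4 = 2.89, which gives power 0.801. The stated 35 reproduces.
- The paired t-test needs 34 for the same target and has power 0.820 at 35.

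The sample size therefore belongs to a within-group change, not to an association.

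**2. Can the paired test tell the two literature positions apart?** Let K be a standardised kyphosis measure and D the standardised change in balance, with D = d + ρK + √(1 − ρ²)E, where E is independent standard normal noise. Whatever ρ is, D has mean d and variance ρ² + (1 − ρ²) = 1. The paired test uses only D, so its behaviour cannot depend on ρ. Simulation (20,000 runs, n = 35, two-sided 0.05) agrees:

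| Mean change d | Correlation ρ | Paired test significant | Correlation test significant |
|---|---|---|---|
| 0 | 0 | 4.9% | 4.9% |
| 0 | 0.5 | 4.9% | 88.3% |
| 0.5 | 0 | 82.0% | 4.9% |
| 0.5 | 0.5 | 82.1% | 88.4% |

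The paired column follows d and ignores ρ; the correlation column does the reverse. The value d = 0.5 is the planned effect size; ρ = 0.5 is an assumption chosen for illustration.

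**3. How much does a non-significant balance change say?** The article gives no expected balance effect other than the general 0.5, so smaller values here are assumptions. Paired t-test power at n = 35 is 0.407 for a standardised change of 0.3 and 0.210 for 0.2. Non-significance then occurs in 1 − 0.407 = 59% and 1 − 0.210 = 79% of studies. A null result is weak evidence even about balance change, before any step to kyphosis.

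**4. What would a direct association analysis deliver at n = 35?** Using Fisher's z, the standard error is 1/√(35 − 3) = 0.177.
- An observed r of 0 has a 95% interval of tanh(±1.96 × 0.177) = ±0.33.
- Power at an assumed r of 0.3 is Φ(0.3095 × √32 − 1.96) = Φ(−0.21) = 0.42.
- Over a range of assumed r, power is 0.21 (r = 0.2), 0.42 (0.3), 0.67 (0.4) and 0.87 (0.5).
- The smallest r detectable with 80% power is tanh((1.96 + 0.84)/√32), about 0.46.

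**The case against.** The strongest defence is that the promise to examine these aspects may rest on the correlations announced in sections 2.4, 3 and 4 rather than on the t-test, and that a condensed article may leave the choice of variables to a fuller document. This stands in part: an intent to correlate is there, and the remedy can build on it. It does not rescue the sentence at issue, which names the end-versus-baseline comparison as its means. More detail on that comparison would not turn it into a test of association.

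The wording is also loose. The established conclusions could be read as conclusions of this study. The two opposing findings immediately before are the more natural referent, but that remains a reading.

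Three stronger inferences are tempting, and the article does not support them:
- **A p-value rule.** A reader might infer that significance will be counted for one side and non-significance for the other. No section says so. The risk of misreading follows from the stated use of the comparison; it is not a written rule.
- **A contradiction over programme design.** The same sentence says the comparison helps to design an individualised programme, whereas section 2.3 builds each plan at the start: "Following the parameters obtained during the initial assessment, the physiotherapist will develop a personalized exercise plan". If the phrase means future programmes, as the closing aims in sections 4 and 5 suggest, nothing conflicts.
- **Proof that no sagittal posture measure will be analysed.** The GaitOn parameters are not listed in full, and section 2.4.4 says its report covers axial deviations. The article names no kyphosis angle, but that does not show that none will exist.

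**Conclusion.** The point holds as a minor one. If the established conclusions are the two cited kyphosis-balance findings, the comparison named to support one of them carries no information on which is right. This follows from the form of the test and does not depend on any assumed effect size. The figures for small balance changes and for the correlation are illustrations under assumed values; they show that a null result should not be read as no relationship, and that a direct analysis in 35 patients would be imprecise. The defect is confined to a secondary interpretive aim.

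**What to change.** 1. In section 4, remove the clause about supporting an established conclusion from the sentence on the before-after balance comparison. Report that comparison as mean change with its 95% CI, and interpret it only as change over the programme period.
2. If the posture-balance question is kept, answer it through the correlation analysis already intended in sections 3 and 4. Name a posture variable that the trial records, for example the lateral-view shoulder angle, and the stabilometry parameter it is paired with. Describe it as that variable and not as kyphosis, unless a kyphosis measure is in fact recorded.
3. Label the analysis exploratory, give the correlation with its 95% CI, and state that p > 0.05 will not be read as no relationship.

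The cost is a wording change and one exploratory analysis line. No new data, visits or patients are needed.

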## 5. Conclusions

This study aims to provide a variety of options for treating patients with PE after complex non-invasive evaluations. The results obtained will help us to detail how physiotherapy influences the treatment of patients with PE and how multidisciplinary cooperation can be recommended in the approach for this disease. Thus, we will consider proposing a protocol for the evaluation and treatment of children and adolescents with PE.

## Figures and Tables

**Figure 1 life-15-01624-f001:**
[figure not shown]
Exemplification of exercise 1: (**a**) initial position; (**b**) final position.

**Figure 2 life-15-01624-f002:**
[figure not shown]
Exemplification of exercise 3: (**a**) initial position; (**b**) final position.

**Figure 3 life-15-01624-f003:**
[figure not shown]
Exemplification of exercise 5: (**a**) initial position; (**b**) final position.

**Figure 4 life-15-01624-f004:**
[figure not shown]
Exemplification of exercise 7: (**a**) initial position; (**b**) final position.

**Figure 5 life-15-01624-f005:**
[figure not shown]
Exemplification of exercise 9: (**a**) initial position; (**b**) final position.

**Figure 6 life-15-01624-f006:**
[figure not shown]
Myotonometric assessment of the left (**a**) and right (**b**) pectoralis major muscle.

**Figure 7 life-15-01624-f007:**
[figure not shown]
Myotonometric assessment of the left (**a**) and right (**b**) upper trapezius muscle.

**Figure 8 life-15-01624-f008:**
[figure not shown]
Myotonometric assessment of the left (**a**) and right (**b**) trapezius medius muscle.

**Figure 9 life-15-01624-f009:**
[figure not shown]
Myotonometric assessment of the left (**a**) and right (**b**) lower trapezius muscle.

**Figure 10 life-15-01624-f010:**
[figure not shown]
Cardiopulmonary exercise assessment.

**Figure 11 life-15-01624-f011:**
[figure not shown]
Static balance assessment (**a**–**c**) (personal collection, patient consent).

**Figure 12 life-15-01624-f012:**
[figure not shown]
Evaluation of posture in anterior (**a**) and posterior view (**b**)—GaitOn (personal collection, patient consent).

**Figure 13 life-15-01624-f013:**
[figure not shown]
Evaluation of posture in left (**a**) and right lateral view (**b**)—GaitOn (personal collection, patient consent).

## Data Availability

The data presented in this study are available on request from the corresponding author ([name]) due to privacy.

## Abbreviations

The following abbreviations are used in this manuscript:

PE	pectus excavatum
CPET	cardiopulmonary exercise testing
CT	computer tomography
EKG	electrocardiogram
VC	vital capacity
VE	ventilatory power
VO_2max_	maximal oxygen consumption
VT1	ventilatory threshold 1
VT2	ventilatory threshold 2
FEF	forced exhaling flow
FEV1	forced exhaling volume per second
FVC	forced vital capacity
